### Primary feasibility outcomes

Study participants enrolment capacity: The study coordinator will monitor weekly enrollment capacity of each of the study sites using the screening and recruitment log. The average number of participants recruited weekly in the respective study sites will be used to evaluate the minimum required time to reach the sample size. The feasibility of the recruitment in a period of 12 months will be considered in order to capture seasonality.Number of refusals: The number of study participants who refuse to participate in the present pilot will be recorded as well as their reasons using the screening and recruitment log. The sample size was calculated including 10% of non-response. In case of a high rate of refusals (>10%), reasons for refusal will be examined in order to improve the recruitment rate in the trial.Perceptions and acceptability: Semi-structured discussion and interview guides will be piloted prior to the start of the study. All revisions made will be noted and incorporated in the final guide. This will allow easy understanding and the percentage of focus group discussions (FGDs) conducted with the minimum required number of participants will be monitored. All FGDs will be conducted with the objective of 100% of completeness.Study visits completion: The percentage of study participants having completed the study follow-up will be calculated. This will be very helpful for the implementation of the trial. A loss to follow-up < 10% will be considered acceptable.Data quality checks: Missing data will be monitored and quantified in this pilot trial. The objective will be to have less than 1% of missing values.Sample size assumptions: Some variables such as the number of doses of IPTp-SP doses taken during pregnancy, normal birth weight (2500g), peripheral malaria infection, and hemoglobin rate will be monitored in both study groups in order to adjust the final sample size calculation.

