#### Secondary clinical outcomes

Safety profile of DHA-PQ and AL: Adverse events for each study drug will be recorded at all schedules and unscheduled visits.Low birth weight. At delivery each baby will be weighted: The prevalence of low birth weight will be compared between the two groups. Low birth weight will be defined as a birth weight less than 2500 g.Maternal peripheral *P. falciparum* infection (microscopy and PCR) at delivery: Malaria case will be defined as the presence of *P. falciparum* at any stage, regardless of clinical signs. The prevalence of peripheral parasitemia at delivery will be compared between the two groups.Maternal anemia at delivery. The prevalence of maternal anemia at delivery will be compared between the two groups. Anemia will be defined as hemoglobin < 11 g/dL.

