#### Intervention group

Prior to each IPTp-SP dose administration, a blood sample will be collected for malaria infection screening using US-RDT and microscopy, Hb measurement, and filter paper confection for parasite genotyping. The date of the next IPTp-SP administration will be planned accordingly and the sequences repeated until delivery. Pregnant women with a positive US-RDT will be treated with a full course of DHA-PQ over 3 days. The first dose will be administered under direct observation during ANC and the subsequent doses of the intervention on days 2 and 3 will be taken unsupervised at home. The treatment observance will be assessed by the field worker at the end of the treatment. In addition, a questionnaire on health and socio-demographic characteristics will be administered as well as a physical examination. A phone call as a reminder will be made 1 week prior to the scheduled date for the second dose of IPTp-SP. If the participant is not reachable, the field worker will visit the household in order to remind the visit date. The objective is to increase the number of IPTp-SP doses per woman.

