### Sample size considerations

We have assumed that this intervention will decrease placental malaria from 40 to 25%, with 80% power and at the 5% significance level, 152 pregnant women per group will be needed. With 10% of lost to follow-up, 170 pregnant women will be needed per arm.

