The secondary clinical outcomes are pilot endpoints to include incidence rates (mean hemoglobin and birth weight), molecular and parasitological endpoints, safety, determinants of poor coverage of IPTP-SP, vector control effectiveness, and adverse events. Adverse events and serious adverse events will be monitored, managed, and recorded during the study. All study participants who receive at least one dose of the study drug will be included in the safety analysis. They will be recorded and tabulated for each treatment group. All parasitological data will be included in the parasitological analyses. For the evaluation of placental malaria and low birth weight in newborns, logistic regression will be performed while for the evaluation of the occurrence of malaria cases in pregnant women during the follow-up, Poisson regression will be implemented. The stratification or adjustment factors will be among others: the number of doses of IPTg-SP, the season of malaria transmission, and the gravidity. A statistical model will be used for the phone reminder by adjusting the number of calls (0, 1, 2) that the woman in the intervention group received before coming to this ANC. In this model, the number of calls for women in the control group will be 0. For the qualitative study, the acceptability will be assessed through focus group discussion and in-depth interviews. Topics covered by the in-depth interviews will comprise many components such as experience and opinions of the trial intervention groups, perceptions of the acceptability of the trial intervention, and implications for implementation. The interview guide will be used to collect data from pregnant women, health care workers, community health care workers, and traditional healers. The theoretical framework of acceptability developed by Mandeep Sekhon, Martin Cartwright, and Jill J. Francis will be used to assess acceptability. In this study, we will analyze the acceptability through the dimension of the burden, ethical consequences, experience, opportunity cost, intention, and affective attitude. The analysis will focus on the barriers and factors limiting adherence to IPTp-SP uptake.

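### The two lists of secondary outcomes need reconciling, and the IPTp-SP dose count, which the reminder is meant to raise, is adjusted for but not compared by randomised group

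*Protocol article*

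**What the plan says.** Under Secondary clinical outcomes the article fixes four outcomes: adverse events of the two study drugs, prevalence of low birth weight (below 2500 g), prevalence of peripheral *P. falciparum* infection at delivery, and anaemia: "The prevalence of maternal anemia at delivery will be compared between the two groups. Anemia will be defined as hemoglobin < 11 g/dL".

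Statistical methods then defines what is meant to be the same set: "The secondary clinical outcomes are pilot endpoints to include incidence rates (mean hemoglobin and birth weight), molecular and parasitological endpoints, safety", followed by "determinants of poor coverage of IPTP-SP, vector control effectiveness, and adverse events". Later in that section, low birth weight is assigned logistic regression and malaria cases during follow-up are assigned Poisson regression.

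On IPTp-SP doses, the Intervention group text under Participant timeline, procedures, and follow-up says of the reminder: "The objective is to increase the number of IPTp-SP doses per woman". Elsewhere the dose count has two roles:

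- Primary feasibility outcomes monitors it in both groups so that the final sample size can be adjusted ("Some variables such as the number of doses of IPTp-SP doses taken during pregnancy" opens that list).
- Statistical methods names it among the potential confounders for the primary outcome, and again among the stratification or adjustment factors.

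Statistical methods also plans a model for the phone reminder. It uses the number of calls received (0, 1 or 2), with control women set to 0.

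**The concern.** Two sections define one set of outcomes differently, so an analyst cannot tell from the article which outcomes are secondary, on what scale, or by what method. One listed endpoint does not correspond to anything that differs between the groups.

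The dose count matters more. Raising it is the stated purpose of one of the three components of the package, and the Introduction gives the gap to be closed: 31.5% of eligible women in Burkina Faso reached at least three doses. If doses enter the models only as a covariate, two things follow. The effect of the package on uptake has no planned estimate. The effect on placental malaria and low birth weight is estimated with the pathway through extra doses held fixed. A pilot meant to inform a main trial should report the first and should not lose part of the second.

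**Working it through.** **1. The plan's own figure.** The section on sample size states: "We have assumed that this intervention will decrease placental malaria from 40 to 25%, with 80% power and at the 5% significance level". With a two-sided test, pooled variance and no continuity correction:

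- mean proportion = (0.40 + 0.25)/2 = 0.325
- n = [1.960·√(2·0.325·0.675) + 0.842·√(0.40·0.60 + 0.25·0.75)]² / 0.15² = 151.9, so 152 per group, as stated
- 152/0.90 = 168.9, so 169, against 170 stated, which is within rounding

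The calculation rests on placental malaria alone, so nothing below changes it.

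**2. The two lists side by side.**

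| Item | Secondary clinical outcomes | List in Statistical methods | Analysis named |
|---|---|---|---|
| Safety | Yes | Yes | Tabulated by treatment group |
| Birth weight | Prevalence below 2500 g | Mean, called an incidence rate | Logistic regression for low birth weight |
| Haemoglobin | Anaemia below 11 g/dL | Mean, called an incidence rate | None for anaemia |
| Peripheral infection at delivery | Prevalence | Only under a general parasitology heading | Not specific |
| Malaria cases in follow-up | No | Only under a general parasitology heading | Poisson regression |
| Determinants of poor IPTp-SP coverage | No | Yes | None as a group comparison |
| Effectiveness of vector control | No | Yes | None |
| Number of IPTp-SP doses by group | No | No | Adjustment factor only |

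Only safety and, broadly, parasitology match. A mean of a continuous measurement has no event count and no person-time, so it is not an incidence rate.

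**3. Vector control.** Intervention description sets ultrasensitive RDTs, DHA-PQ and phone reminders against standard RDTs, AL and no reminder. Neither package contains vector control, and none of the trial procedures from enrolment to delivery measures it. There is therefore no randomised contrast.

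**4. Dose count as a covariate.** Doses accrue after randomisation, and the reminder exists to change them. On an additive scale, write the package effect as D + a·b, where a is the effect of assignment on doses, b the effect of a dose on the outcome, and D everything else. A model that includes doses estimates D at best, so a·b is lost. If the reminder works (a ≠ 0) and doses matter (b ≠ 0), the adjusted estimate is not the combined package effect that Intervention description says will be compared. The documents give neither a nor b, so the loss cannot be sized.

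**5. The reminder model.** It names no dependent variable, and its regressor is calls received, not assignment. An intervention woman who could not be reached by phone is to be visited at home. If unanswered calls are not counted, she has 0 calls, the same code as a control woman, although she was reminded.

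**6. Precision of the missing comparison (illustrative).** Assume 31.5% with at least three doses in both groups.

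- 170 per group: 1.96·√(2·0.315·0.685/170) = 0.099
- 152 per group: 1.96·√(2·0.315·0.685/152) = 0.104

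The 95% half-width is about 10 percentage points either way.

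**The case against.** The case for leaving the text alone has several parts, and some of them stand.

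- *Low birth weight and anaemia.* A reader might infer that both now have two competing definitions, so that the more favourable could be reported. The text does not support this. Statistical methods keeps low birth weight binary through its logistic regression, and Secondary clinical outcomes still fixes the anaemia cut-off, its timing and the comparison between groups. A mean and a prevalence from the same measurement are not rival definitions. The second list is also introduced as things to be included, which need not be exhaustive. What remains is that anaemia has no named analysis and the means carry a wrong label.
- *Uptake.* A reader might infer that the trial never examines uptake, or that a null placental result could not be traced to failed uptake. That goes too far. Doses are monitored in both groups and can be described, determinants of poor coverage are listed, and a reminder model is planned. None of these is a comparison by randomised group, however.
- *Package effects only.* Intervention description rules out comparing individual components. Comparing doses by assignment respects this, because it is a package contrast. Adjusting for doses is what departs from it.
- *Vector control.* The surveillance system in Study setting records access to and use of key disease control interventions, so an observational association is conceivable. The article describes no such analysis, and it would not be a between-group trial endpoint.
- *Condensed article.* A journal article may omit detail, but here two passages that are present disagree, and a covariate role is stated explicitly.

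**Conclusion.** The point holds. The two lists of secondary outcomes differ and must be reconciled. Within it, the consequential part is the dose count: an intended effect of the package is used for adjustment while no comparison by randomised group is planned. The vector control entry lacks a randomised contrast and any described measurement. The incidence-rate label is close to clerical.

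Severity is moderate. The sample size, the randomisation and the definition of the primary outcome are untouched. The adjustment does reach the between-group models, including placental malaria, where dose count is listed as a potential confounder. The conclusion that adjustment removes part of the effect assumes that the reminder changes doses and that doses affect the outcome, both of which the article itself supposes. The ±10 points is the precision of a comparison not yet planned. It assumes that the national 31.5% applies to both groups, and it is not the size of any error.

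**What to change.** (a) Add the number of IPTp-SP doses, and the proportion of women with at least three, as a secondary outcome compared by randomised group. Remove dose count from the adjustment set of every between-group outcome model. If the call-count model is kept, name its dependent variable and label it exploratory, because it conditions on calls received.

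(b) Delete the effectiveness of vector control as a trial endpoint, or label it as descriptive or observational only.

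(c) Use one list in both sections. Keep anaemia below 11 g/dL and low birth weight below 2500 g as the binary secondary outcomes, with an analysis named for anaemia. Give mean haemoglobin and mean birth weight as supporting continuous summaries and drop the incidence-rate label.

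The cost is wording only. Dose counts are already monitored in both groups, haemoglobin and birth weight are already measured at delivery, and no extra participants are needed.

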#### Control group

In case of signs and symptoms suggestive of malaria infection, the nurse will follow the NMCP recommendations. An HRP-2 RDT will be performed and the participant treated with a full course of AL if positive. The first dose will be administered under direct observation at the ANC clinic, and the subsequent doses on days 2 and 3 will be taken unsupervised at home. Before treatment and regardless of the RDT result, the nurse will systematically collect a blood sample for hemoglobin measurement, microscopy, and filter paper for subsequent genotyping. Blood slides will be read after and treatment will be based on the result of RDTs as recommended by the NMCP in peripheral centers. In addition, a questionnaire on health and socio-demographic characteristics will be administered as well as a physical examination. No reminder will be used for the next ANC visit/IPT-SP dose date.

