### Follow-up

#### Intervention group

One month after the first ANC visit with the first IPT-SP dose administration, the participant will be invited to the health facility for screened for malaria infection using the US-RDT. From that and at monthly intervals up to the last week of gestation, the pregnant women will be encouraged to visit the ANC clinic where the study nurse will perform a systematic screening using US-RDT and treatment with a full course of DHA-PQ if positive. The first dose will be administered under direct observation during ANC and the subsequent doses on days 2 and 3 will be taken unsupervised at home. The assessment of the treatment observance will be checked by the field worker at the end of the treatment. Before treatment and regardless of the US-RDT result during scheduled and unscheduled visits, the nurse will systematically collect a blood sample for hemoglobin measurement, microscopy, and filter paper for subsequent genotyping.

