#### Control group

After the first IPT-SP dose administration, the date of the second one will be scheduled. No additional screening will be performed in this group. In case of signs and symptoms suggestive of malaria infection, the nurse will follow the NMCP recommendations. An HRP-2 RDT will then be performed and the participant treated with a full course of AL if positive. The first dose will be administered under direct observation during ANC and the subsequent doses on days 2 and 3 will be taken unsupervised at home. Before treatment and regardless of the RDT result during scheduled and unscheduled visits, the nurse will systematically collect a blood sample for hemoglobin measurement, microscopy, and filter paper spot for subsequent genotyping.

Irrespective of the study group, field workers will visit the treated participant on day 3 (final day of treatment) in order to assess uptake and compliance to treatment by administering a short questionnaire to check the empty packaging of the treatment. If the woman is severely ill at the time of the visit (e.g., from malaria or other causes and/or from complications from the pregnancy), they will be referred to the health facility for further care. In order to minimize the non-response in group 2, we will collect a blood sample (microscopy and blood spots) in all pregnant women regardless of the study group at fixed schedule visits: day 60 and day 80.

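### The safety set admits only women given a study drug, on a different trigger in each arm, so the by-group adverse event table is not a randomised comparison

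*Protocol article*

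**What the plan says.** Statistical methods sets the safety population: "All study participants who receive at least one dose of the study drug will be included in the safety analysis". The next sentence gives the display: "They will be recorded and tabulated for each treatment group". No safety analysis of all randomised women is described.

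The article does not define *study drug*. The nearest guide is the first secondary clinical outcome: "Safety profile of DHA-PQ and AL: Adverse events for each study drug will be recorded at all schedules and unscheduled visits". That ties the term to DHA-PQ and AL. The first exclusion criterion mentions sulphonamides and the study drugs side by side, which hints that SP is not one of them but does not settle it.

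Neither DHA-PQ nor AL is given at randomisation. Under Follow-up, in the intervention group "the study nurse will perform a systematic screening using US-RDT and treatment with a full course of DHA-PQ if positive". For controls, testing waits for symptoms: "In case of signs and symptoms suggestive of malaria infection, the nurse will follow the NMCP recommendations". A woman whose HRP-2 test on that occasion is positive receives AL. The same section adds for controls: "No additional screening will be performed in this group".

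**The concern.** Receiving a study drug is something that happens after randomisation, and the two arms reach it by different routes. An intervention woman qualifies through a positive routine screen, with or without symptoms. A control woman qualifies only if she has symptoms and then tests positive. The Introduction and the Discussion both describe infected pregnant women in such areas as mostly free of symptoms. By the article's own account, then, the DHA-PQ column will hold mainly asymptomatic women and the AL column symptomatic patients.

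Two things are at stake. First, a difference in adverse event rates between the columns may reflect who was treated and not what the treatment did. Second, women never treated are outside the set. These include controls whose infections were never detected, so any serious events or pregnancy losses they have would not enter the between-group table. The Intervention description says that the packages are to be compared as wholes and their components are not. A treated-only table by group is in effect a table of one drug beside the other.

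**Working it through.** **The denominator.** Sample size considerations assumes placental malaria of 40% against 25%, 80% power and 5% significance (taken as two-sided). With pooled variance and no continuity correction:

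n = [1.960 × √(2 × 0.325 × 0.675) + 0.842 × √(0.40 × 0.60 + 0.25 × 0.75)]² / 0.15² ≈ 152 per group, as stated.

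Inflating for 10% loss gives 152 / 0.90 = 168.9, or 169, against the stated 170. These figures are sound. They matter here only because they fix the denominator at 2 × 170 = 340.

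**Size of the safety set.** The article gives no US-RDT positivity rate, no treatment rate for either arm and no expected size for the safety set. All three inputs below are therefore assumptions:
- k, screens per intervention woman: 4 to 6. Entry at 16 to 24 weeks with four-weekly visits to an assumed 40 weeks gives (40 − 24)/4 = 4 to (40 − 16)/4 = 6.
- p, positivity per screen: 5% to 40%, taken as constant and independent between screens.
- c, share of controls treated for symptomatic malaria: 5% to 40%.

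The share of intervention women treated at least once is s = 1 − (1 − p)^k. The set holds 170 × (s + c) women, and the share left out is 1 − (s + c)/2.

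| k | p | c | Intervention in set | Control in set | Total of 340 | Left out |
|---|---|---|---|---|---|---|
| 4 | 5% | 5% | 31.5 | 8.5 | 40 | 88% |
| 5 | 10% | 10% | 69.6 | 17 | 87 | 75% |
| 5 | 20% | 20% | 114.3 | 34 | 148 | 56% |
| 5 | 30% | 30% | 141.4 | 51 | 192 | 43% |
| 6 | 40% | 40% | 162.1 | 68 | 230 | 32% |

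The first and last rows are the extremes of the grid. In all five rows the intervention arm supplies more women than the control arm, by a factor of about 2.4 to 4.1.

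**When would a majority be left out?** Only if s + c < 1, that is, p < 1 − c^(1/k). With k = 5 the limit is about 37% for c = 10%, 27% for c = 20% and 21% for c = 30%.

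**What selection alone can do.** Suppose neither drug has any effect on an event that is recorded in 60% of symptomatic and 10% of asymptomatic women (assumed). All treated controls are symptomatic, so their rate is 60%. If a fraction f of treated intervention women are symptomatic, their rate is 0.60f + 0.10(1 − f):
- f = 10%: 15%
- f = 20%: 20%
- f = 30%: 25%

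The gap of 35 to 45 percentage points is produced entirely by the entry rule. The figures are illustrative. They show that the mechanism can be large, not that this is its size in the trial.

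**The case against.** The strongest reply is that a treated-only set is the usual population for describing a drug's tolerability. The article promises a safety profile with events recorded and tabulated, whereas for low birth weight, peripheral infection and anaemia it speaks of comparing the groups. This is fair: no formal test of DHA-PQ against AL is stated, and a reader who infers one goes beyond the text. But the table is laid out by treatment group, it is the only safety analysis described, and it will be read across its columns.

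Four further points limit how far the concern can be pushed.

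- A reader might infer that most randomised women are dropped. The article has no rate from which to derive this. It is plausible over much of the assumed range but fails at higher positivity, and the assumed 40% placental malaria without the intervention does not rule such positivity out.
- *Study drug* is undefined, and SP is scheduled in both arms. If SP counted, almost nobody would be left out. The restriction to DHA-PQ and AL is the better-supported reading, not a stated fact.
- A reader might infer that DHA-PQ is bound to look safer. That requires malaria symptoms to be counted as adverse events, which the article does not say. Repeated courses, monthly contacts and reminders could raise recorded events in the intervention arm instead.
- A reader might infer that harms in untreated women go uncounted altogether. They do not: adverse events are monitored during the study, an independent DSMB reviews all safety data, and the delivery outcomes are compared by group without restriction to treated women. None of this supplies a by-group safety analysis of all randomised women.

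The statistical analysis plan is not shown and might contain such a table. The point remains because the article does not leave the safety population open: it states one.

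**Conclusion.** Wrong as written. With *study drug* read as DHA-PQ or AL, entry to the safety set depends on a post-randomisation event with a different trigger in each arm. The by-group table is then not protected by randomisation and excludes all untreated women. This conclusion needs only the two treatment triggers, and no rate.

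The size of the exclusion is not fixed by the document: about 32% to 88% of 340 women over the assumed ranges, with unequal shares by arm. The direction of the resulting bias is uncertain. If malaria symptoms are recorded as adverse events, it would tend to run against AL. If the term was meant to include SP, the set is close to everyone randomised and the remaining fault is an undefined term on which the whole safety population turns.

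**What to change.** 1. Define *study drug*, saying explicitly whether SP is included.
2. Make the between-group safety comparison in all randomised women by assigned group: adverse events, serious adverse events and pregnancy losses from enrolment to delivery, per woman and per person-time.
3. Keep the treated-women table as a descriptive profile of each drug, without a between-drug comparison, and note beside it that recipients differ in symptom status.

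The cost is some wording and one extra analysis. Adverse events are already to be recorded at all scheduled and unscheduled visits; the sponsor should confirm that this covers women who never receive a study drug. One downside remains: the intervention group's more frequent contacts may raise the recording of minor events. Serious adverse events and pregnancy losses, which depend less on contact frequency, should therefore lead the comparison.

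### The Poisson comparison of malaria cases during follow-up is not tied to samples taken alike in both groups, so unequal sampling may shrink a true benefit or, in some scenarios, reverse it

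*Protocol article*

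**What the plan says.** **Analysis.** Under Statistical methods the protocol article says that "for the evaluation of the occurrence of malaria cases in pregnant women during the follow-up, Poisson regression will be implemented". It adds: "All parasitological data will be included in the parasitological analyses". The stratification or adjustment factors include, among others, "the number of doses of IPTg-SP, the season of malaria transmission, and the gravidity". The number of tests or visits is not named. The section does not say which test or which samples define a case during follow-up.

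**Intervention group (Follow-up).** "From that and at monthly intervals up to the last week of gestation", women are encouraged to attend the clinic, where "the study nurse will perform a systematic screening using US-RDT and treatment with a full course of DHA-PQ if positive". Microscopy and filter-paper samples are also taken at scheduled and unscheduled visits. A phone call, or a household visit if the woman cannot be reached, reminds her of the next visit (Participant timeline, procedures, and follow-up).

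**Control group (Follow-up).** "No additional screening will be performed in this group". A standard HRP-2 rapid test is done only when there are signs or symptoms, and there are no reminders. The same section nevertheless has microscopy and filter-paper samples collected at scheduled and unscheduled visits. It also plans microscopy and blood spots "in all pregnant women regardless of the study group at fixed schedule visits: day 60 and day 80".

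**The concern.** A count of detected infections depends on how many infections occur and on how often, and how sensitively, one looks for them. Here the looking differs by design. One group is tested monthly whether or not symptoms are present, with reminders that raise attendance. In the other group the rapid test is triggered by symptoms. The Discussion says that infection in pregnancy is often asymptomatic, that current rapid tests miss low parasitemia, and that monthly screening is meant to improve case detection. More detected cases per true infection in the intervention group is thus an intended feature of the package, yet detected cases are also analysed as an outcome.

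The rule to use all parasitological data is fixed in the text, so an analysis plan that follows it takes over the problem. The Discussion expects this pilot to give preliminary evidence of efficacy, including on peripheral infection. A follow-up rate ratio pulled towards or beyond 1 by sampling alone would misinform that reading.

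**Working it through.** The protocol gives no figure for this analysis. Its only sample size calculation, 152 women per group, concerns placental malaria and plays no part here. The check asks what rate ratio the count would show when the true ratio is known.

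**Inputs**
- Four monthly tests in the intervention group. Entry is at 16 to 24 weeks (Inclusion criteria). With delivery assumed near 40 weeks, 16 to 24 weeks remain, or about 4 to 6 monthly visits; 4 is the low end.
- Positivity *p* per sample of 10%, 15% or 20% without any effect (assumed).
- 0.3 symptomatic episodes per control woman, counted in addition to scheduled positives (assumed).
- True rate ratio of 0.60 for both kinds of case (assumed).
- Equal test sensitivity in both groups (assumed).

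**Formulas, cases per woman**
- Intervention with *m* samples: 0.60 × (*m* × *p* + 0.3)
- Control with *k* samples: *k* × *p* + 0.3
- Apparent ratio: the first divided by the second

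| Scenario | *m* | *k* | Intervention at 10 / 15 / 20% | Control at 10 / 15 / 20% | Apparent ratio |
|---|---|---|---|---|---|
| A. Microscopy at the same four scheduled visits | 4 | 4 | 0.42 / 0.54 / 0.66 | 0.70 / 0.90 / 1.10 | 0.60 / 0.60 / 0.60 |
| B. Controls attend three visits | 4 | 3 | 0.42 / 0.54 / 0.66 | 0.60 / 0.75 / 0.90 | 0.70 / 0.72 / 0.73 |
| C. Controls contribute only day 60, day 80 and symptomatic samples | 4 | 2 | 0.42 / 0.54 / 0.66 | 0.50 / 0.60 / 0.70 | 0.84 / 0.90 / 0.94 |
| D. As C, with day 60 and day 80 added to the intervention group's monthly tests | 6 | 2 | 0.54 / 0.72 / 0.90 | 0.50 / 0.60 / 0.70 | 1.08 / 1.20 / 1.29 |

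For example, D at 10%: 0.60 × (6 × 0.10 + 0.3) = 0.54; 2 × 0.10 + 0.3 = 0.50; 0.54 / 0.50 = 1.08.

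**Second check, with no true difference.** Give the intervention group *m* tests. Give controls two fixed samples, plus a share *s* of the infections at the other *m* − 2 occasions, found through symptoms. The apparent ratio is *m* / (2 + (*m* − 2)*s*).
- *m* = 4, *s* = 50%: 4 / 3 = 1.33
- *m* = 6, *s* = 10%: 6 / 2.4 = 2.50

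Multiplying by a true ratio of 0.60 gives 0.80 to 1.50. This spans dilution and reversal, as C and D do.

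**Like-for-like samples.** With the same three occasions in both groups (day 60, day 80, delivery), the ratio is (3 × 0.60*p*) / (3*p*) = 0.60, and 1.0 when there is no true difference.

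**The case against.** The strongest reply is that the control group is not left unsampled. Follow-up, Control group plans microscopy and filter paper at scheduled and unscheduled visits, plus the two fixed samples in everyone, and the all-data rule brings these in. If attendance is equal and cases are defined by microscopy, scenario A applies and there is no bias. This stands, and it limits the point.

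A reader might infer that the plan sets actively screened women against women tested only when symptomatic, so that a benefit is bound to appear as harm. With no scheduled or fixed control samples counted, the same inputs would give 0.42 / 0.30 = 1.4 up to 0.66 / 0.30 = 2.2. The protocol does not support that reading, because it requires discarding control samples that the protocol plans to collect and include.

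Three further objections also hold:
- The definition of a malaria case as any *P. falciparum* regardless of symptoms is given under Secondary clinical outcomes for infection at delivery, by microscopy and PCR. Nothing says that positive ultrasensitive rapid tests enter the Poisson count. Blood films and PCR are read blind (Randomization and blinding; Clinical outcomes).
- Offset, overdispersion and repeated positives in one woman are details that an article may leave to the analysis plan. The adjustment list is open-ended.
- Primary feasibility outcomes names peripheral malaria infection as an input to the final sample size, not this rate ratio. It is not shown that the ratio would feed the main trial's calculation.

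What the reply does not remove is that the number of samples differs by group through monthly invitations and reminders, while the stated rule neither restricts the comparison to common samples nor names an adjustment for the number of tests.

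**Conclusion.** The concern holds as a risk of ascertainment bias against the intervention in one secondary analysis. Against an assumed true ratio of 0.60, the apparent ratio ranges from 0.60 (equal scheduled sampling), through 0.84–0.94 (controls supply only the two fixed samples and symptomatic episodes), to 1.08–1.29 (the fixed samples are also extra tests in the intervention group). Dilution is the usual result where controls are sampled less often; reversal is possible but not established. Every input except the range of visit numbers is assumed, and equal test sensitivity is taken throughout. If positive ultrasensitive tests were counted as cases, the distortion would be larger by an amount the protocol gives no figures to estimate.

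Placental malaria and peripheral infection at delivery are sampled by the same procedure in both groups and are not affected. The point deserves correction before analysis but does not threaten the trial's main result.

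**What to change.** 1. Restrict the between-group comparison of infection to samples taken on the same schedule in both groups (day 60, day 80 and delivery) and read by the same blinded microscopy or PCR. Use a repeated-measures model, such as generalized estimating equations with robust standard errors. The delivery sample is already a secondary outcome in its own right, so the overlap should be stated.
2. Compare symptomatic, confirmed episodes separately, per person-time.
3. Report positives from the monthly ultrasensitive screening descriptively, in the intervention group only.
4. Reconcile, within Follow-up, Control group, the statement that there is no additional screening with the systematic sampling at scheduled visits, so that it is clear which control samples will exist.

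The cost is a change of wording, since these samples are already planned in both groups. The drawback is that some samples taken only in the intervention group leave the comparison, with some loss of information.
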